### Mixed effects analysis

3.2

A mixed effects model will be used to assess the mean differences between the groups for the outcomes considered. The fixed effects are between‐participant variables such as age, sex, BMI, symptom management and footwear. These models incorporate time as the random effects which is a within‐subject variable. All assumptions for mixed effects modelling will be checked. As most of the outcome measures will be considered as continuous, normality and homogeneity of variance assumptions will be assessed. If these assumptions are violated, alternative modelling approaches will be considered. Effect modification by age, BMI and sex will be explored using likelihood ratio tests, taking into consideration the sample sizes of the subgroups. Strata‐specific results will be reported if the *p* value for the interaction terms is < 0.1, and if at least one of the observed associations from the strata‐specific models are statistically significant at *p* ≤ 0.05. Results from these models will be presented as estimated effect sizes (both unadjusted and adjusted), standard errors, 95% confidence intervals and *p* values. All statistical analyses will be performed using the latest version of Stata (StataCorp, College Station,TX, USA).

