### Sample size

2.4

Sample size was calculated based on the primary outcome measure, the University of Wisconsin Running Injury and Recovery Index (UWRI) [12]. Using a power of 80%, previously reported standard deviation of 6.7 [13], medium effect size (Cohen's *d* = 0.75) of 5 points on the 36‐point UWRI [14] and a significance level set at *α* < 0.05, we estimated using GPower 3.1 (Kiel University, Germany) that a total of 60 participants (i.e., approximately 30 per group) will be required. When estimating sample size we were limited with data available and have opted to use the medium effect size for our estimation. To allow for any imprecision in these estimates, we will have a recruitment target of 32 participants per group.

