### Assessments and data collection sessions

2.8

Once participants are determined to be eligible for this study, they will undergo primary and secondary outcome measurements at baseline, 2 weeks, 4 weeks, and 8 weeks. Participants will attend five data collection sessions: session 1 (baseline), session 2 (week one), session 3 (week two), session 4 (week four) and session 5 (week eight). Participants in both groups will receive similar time at each data collection session, with the duration of each session measured for comparison at the end of the trial. Figure 1 outlines the flow of participants through the trial.

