### Descriptive analysis

3.1

Differences between the control and intervention group in demographic and clinical characteristics and for the primary and secondary outcome measures (2, 4, and 8 weeks) will be described and assessed using *t* tests for continuous and chi‐square for categorical variables. If after assessment of the assumptions of the *t* test (such as the homogeneity of variance) are violated, we will use alternatives such as the Welch's test with Satterhwaite approximation as a sensitivity analysis. For cell counts <5, *p* values from chi‐square tests will not be reported.

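### Neither the t tests nor the mixed model is specified to adjust for the baseline UWRI score that every participant provides before allocation

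*Protocol article*

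**What the plan says.** The abstract makes UWRI at week 4 the primary outcome. Section 2.8 says of eligible participants that "they will undergo primary and secondary outcome measurements at baseline, 2 weeks, 4 weeks, and 8 weeks", and section 2.9 places the baseline measurements before allocation. Every randomised participant should therefore have a baseline UWRI score.

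Two analyses are described:

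- **Section 3.1 (Descriptive analysis).** The groups are compared on demographic and clinical characteristics, and the "primary and secondary outcome measures (2, 4, and 8 weeks) will be described and assessed using" t tests for continuous variables. No baseline term is mentioned.
- **Section 3.2 (Mixed effects analysis).** "A mixed effects model will be used to assess the mean differences between the groups for the outcomes considered". The fixed effects are introduced by way of example: sex, age, BMI, footwear and symptom management. Time is described as a within-subject variable entering as a random effect. The section promises unadjusted and adjusted results but does not say which is primary.

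Change from baseline is mentioned in neither section. Randomisation is stratified by sex only (section 2.1), so the design does not balance baseline UWRI. The sample size in section 2.4 is a plain two-group comparison of means.

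**The concern.** The pre-randomisation value of an outcome is usually among its strongest predictors. Here it costs nothing to use, since it is already collected. The article goes far enough to name covariates, and the one most likely to explain week-4 UWRI is not among them.

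Two things are at stake. The first is precision: leaving baseline out keeps variance in the week-4 comparison that could be removed. The second is chance imbalance: with about 32 runners per group, the arms may differ at baseline by an amount that is not trivial beside the 5-point target, and an unadjusted week-4 difference carries part of that gap. The same reasoning applies to the secondary outcomes measured at baseline, although the documents give no figures from which to size it.

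**Working it through.** **Inputs from section 2.4**

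- Power: "Using a power of 80" per cent.
- Alpha: "a significance level set at" 0.05. Sidedness is not stated.
- SD: "previously reported standard deviation of 6.7".
- Difference: "of 5 points on the 36‐point UWRI".
- Result: "a total of 60 participants (i.e., approximately 30 per group) will be required". The recruitment target is 32 per group.

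**Assumptions, not in the documents**

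- The baseline to week-4 correlation r of UWRI, taken over 0.2 to 0.7.
- The SD of 6.7 is that of the week-4 score.
- A 15% loss, for illustration only: 32 × 0.85 = 27.2, so 27 per group.

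**Step 1: reproduce the plan's figure.** d = 5/6.7 = 0.746. A two-sided noncentral t test at 0.05 needs 30 per group (power 81.1%), a total of 60. This matches the plan. A one-sided test would need 23 per group, so two-sided is the reading that fits.

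**Step 2: unadjusted power at the target.** With 32 per group the noncentrality is 0.746 × √(32/2) = 2.985 on 62 df. Power is 83.6%.

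**Step 3: power with baseline adjustment.** The residual SD becomes 6.7 × √(1 − r²), so residual variance falls by the fraction r². One df is lost for the covariate (61 df). The standard error of the week-4 difference is residual SD × √(2/32).

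| r (assumed) | Variance removed | Residual SD | SE | 95% CI half-width | Power, 32 per group |
|---|---|---|---|---|---|
| none | 0% | 6.70 | 1.68 | 3.35 | 83.6% |
| 0.2 | 4% | 6.57 | 1.64 | 3.28 | 85.0% |
| 0.3 | 9% | 6.39 | 1.60 | 3.20 | 86.9% |
| 0.4 | 16% | 6.14 | 1.54 | 3.07 | 89.3% |
| 0.5 | 25% | 5.80 | 1.45 | 2.90 | 92.4% |
| 0.6 | 36% | 5.36 | 1.34 | 2.68 | 95.7% |
| 0.7 | 49% | 4.78 | 1.20 | 2.39 | 98.4% |

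**Step 4: with the assumed 15% loss (27 per group).** Unadjusted power is 76.8%. With adjustment it is 80.5% at r = 0.3 and 87.4% at r = 0.5. Section 2.4 states no dropout rate; it raises 60 to 64 to cover imprecision in the estimates.

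**Step 5: chance imbalance.** If the baseline SD is also 6.7 (assumed), the baseline difference between groups has SE 6.7 × √(2/32) = 1.68. A gap of more than 2 points in either direction then arises in about 23% of such trials, and of more than 3 points in about 7%. With equal SDs, a baseline gap g moves the expected unadjusted week-4 difference by r × g. For g = 3 this is 0.9, 1.5 or 2.1 points at r = 0.3, 0.5 or 0.7, against the 5-point target.

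**The case against.** The other side has several good points.

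- **The covariate list is open.** Section 3.2 offers its fixed effects as examples, and the article condenses a fuller document. A reader might infer that baseline UWRI has been ruled out of the model. The text does not support that: it is not named, which is weaker. This stands, and it is why the point is that adjustment is not specified.
- **Baseline may enter as a repeated response.** Section 2.8 counts baseline among the measurement times, and section 3.2 does not exclude it from the modelled times. With a suitable group-by-time contrast, baseline differences would be accounted for. The text specifies neither the baseline response nor such a contrast, so this remains possible but unstated.
- **The t tests are descriptive.** They sit under that heading, and the mixed model is the analysis said to assess group differences. Unadjusted t tests beside an adjusted model are no error. However, no sentence says which estimate is primary.
- **Nothing stated is invalid.** A reader might infer bias, an inflated type I error or a faulty sample size. None follows. Randomisation keeps the unadjusted estimate unbiased on average, its standard error already covers chance imbalance, and the stated 60 reproduces.
- **The gain may be modest.** Entry requires pain of at least 3 out of 10 and excludes those unable to run (section 2.3). This may narrow the baseline spread and lower r. At r of 0.3 or below the gain is about 3 percentage points or less. The comparison in the table is also with a bare t test; covariates already named may capture part of the gain.

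These points limit the size and tone of the concern. They do not remove it: where an article names its covariates, leaving the baseline outcome unnamed is worth settling before the data are unblinded.

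**Conclusion.** The point holds as a matter of efficiency and clarity. As written, neither analysis is specified to adjust for baseline UWRI. For the t tests the text is plain. For the mixed model it is an omission from an open list, so confidence there is moderate.

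At 32 per group the plan meets its 80% target without adjustment, and its sample size remains sufficient, indeed conservative, after the change. What is given up ranges from little (about 1 to 3 percentage points of power at r = 0.2 to 0.3) to substantial (about 9 points at r = 0.5 and 15 at r = 0.7). It matters most if participants are lost, since at the assumed 15% loss unadjusted power falls below 80%. All these sizes rest on an assumed correlation, on reading 6.7 as the SD of the week-4 score and, for the imbalance figures, on the same SD at baseline.

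**What to change.** In section 3.2, and in the analysis plan:

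1. Name the baseline value of each outcome as a covariate in its model, with the follow-up visits (weeks 2, 4 and 8) as responses. A repeated-measures model that includes baseline as a response, constrained equal between groups, serves the same purpose and is equally acceptable.
2. Exempt global rating of change and ATEMPT, which have no meaningful baseline value.
3. State that the baseline-adjusted week-4 UWRI contrast is the primary estimate and that the t tests in section 3.1 are descriptive only.

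The cost is a sentence or two, settled before unblinding. No new data, visits or participants are needed, and the sample size can stay as it is.

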#### Symptom management advice

2.6.2

If participants have been using oral or topical medicines (e.g., analgesia, anti‐inflammatories, etc.) to assist with managing their symptoms, they will be advised to continue with their usual use of medicines. If they have not been using medicines in the management of their symptoms, they will be instructed to not commence using medicines to manage their symptoms during the trial. Participants will be requested to document all use of medicines used to manage MTSS symptoms.

Participants will be instructed on the use of a foam roller/release ball on their posterior lower leg muscles. They will be advised to do this a minimum of twice per week, spending approximately 5 minutes on each leg.

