#### Footwear and foot orthoses advice

2.6.3

Participants' running footwear, and foot orthoses if being used for running, will be assessed to determine if appropriate in the opinion of [name] (e.g., running footwear is not showing signs of excessive wear [either on visual observation of the sole of the shoe, or on assessment of foam to ensure no areas of significant collapse]; orthoses have not been recently prescribed, or the participant reports an increase in symptoms or discomfort whilst wearing orthoses). If considered appropriate, participants will be advised to continue to run in the same footwear and foot orthoses for the duration of the trial. If their running footwear is determined to require replacement due to excessive wear, or it is determined to require replacement during the trial, it will be recommended that participants purchase the same footwear model. If the same footwear model cannot be sourced, then a similar replacement model will be recommended following discussion with [name].

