### Session 1 (baseline)

2.9

A clinical examination will be performed to ensure that participants have a clinical diagnosis of MTSS [2]. Participants will complete a questionnaire to obtain information concerning the presentation of their symptoms (lower limb affected, duration of symptoms). Participants' age, sex, gender, height, and mass will be recorded. Data regarding running participation (current running volume, running training history) will also be obtained. During the baseline assessment, participants will have primary and secondary outcome measurements (see ‘outcome measures’ section for details regarding all outcomes) collected prior to being allocated to their intervention.

Participants will receive the first 2 weeks of their strengthening program, with exercises demonstrated by [name] ([name]). Participants will then be supervised completing each exercise to ensure appropriate technique and safe execution of the program. Instructions regarding the determination of exercise dosage will be given. Participants will be provided with a Garmin running watch for the duration of the trial if they do not own one that meets the needs of the study. Participants in both groups will have 2D video footage of their running collected. Participants allocated to the intervention group will be receive a running retraining intervention to reduce their running step length, and a step rate target for overground running will be determined. The target step rate will be programmed into participants Garmin watch to enable real‐time feedback. No further instructions will be provided to participants allocated to the control group; however, they will be instructed that we will be documenting how their running mechanics change throughout the duration of the trial.

Participants will be instructed on the use of software, as described previously, to record adherence with their strengthening program and how to document their symptom management strategies (e.g., ice, oral medications, etc.). They will also be given further information regarding the secondary outcome measure ‘worst pain experienced during a run’ to be recorded on a NPRS. Participants will discuss their current symptoms and run load with [name], and an appropriate run program for the first 2 weeks will be outlined.

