### EVALUATION OF INTERVENTION ADHERENCE

2.15

Adherence to interventions and training load will be documented throughout the trial. Participants will be required to record their adherence to the strength program, symptom management advice, response to their run sessions, and run volume via a custom‐built software (The Injury Clinic Pty Ltd., Geelong, Australia) installed on their phone. Adherence to a reduction in running step length will be confirmed at sessions 1 to 5, and the step rate required to achieve the target step length will be recorded by the Garmin running watch for each run. Adherence will be considered to be acceptable if participants in both the intervention and control groups complete 80% of their programmed strength sessions, and if participants in the intervention group complete 80% of their running retraining sessions [27]. Participants strength program will be considered complete if a minimum of 8 out of 12 exercises have been completed within each session.

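### The adjusted model includes symptom management, and less importantly footwear, without fixing them at pre-randomisation values, so the adjusted effect may be biased if in-trial values are used

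*Protocol article*

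**What the plan says.** Section 3.2 (Mixed effects analysis) lists the fixed effects as "variables such as age, sex, BMI, symptom management and footwear" and calls them between-participant variables, in contrast to time. Results are to be given unadjusted and adjusted, and neither is named as primary. The abstract and the Discussion promise analysis by intention to treat.

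On symptom management:
- Section 2.6.2 has existing users of medicines carry on as usual. Of non-users it says "they will be instructed to not commence using medicines to manage their symptoms during the trial". It then states: "Participants will be requested to document all use of medicines used to manage MTSS symptoms". Foam rolling is also part of the advice.
- Section 2.9 (Session 1) has participants taught "how to document their symptom management strategies" in the study software, with ice and oral medicines as examples.
- Section 2.15, on documentation throughout the trial, says: "Participants will be required to record their adherence to the strength program, symptom management advice".
- The data that section 2.9 lists for baseline are symptom presentation, age, sex, gender, height, mass and running participation, besides the outcome measures. Neither medicine use nor footwear is among them.

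On footwear, section 2.6.3 keeps the same shoes and orthoses by default. Shoes may be replaced by the same or a similar model if worn at the outset, "or it is determined to require replacement during the trial".

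**The concern.** Randomisation protects a comparison only as long as the model does not condition on something that allocation may have changed. Use of medicines, ice and self-release plausibly responds to pain, and pain is what retraining is meant to reduce. A person's in-trial use is then partly a consequence of treatment or of the outcome itself. Adjusting for it takes out part of the effect under study, and it also opens a path through anything that drives both use and UWRI score.

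At stake is the adjusted estimate. The plan would print it beside the unadjusted one without saying which answers the trial's question, so an estimate that does not measure the effect of assignment could become the headline.

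**Working it through.** **1. The plan's own figure.** Section 2.4 gives a difference of 5 points, SD 6.7, power 80% and alpha 0.05. The standardised effect is 5/6.7 = 0.746. A two-sided two-sample t test needs 29.18 per group, rounded up to 30, so 60 in total. This matches the plan. Power is 81.1% at 30 per group and 83.6% at the target of 32. The concern leaves this figure unchanged; 5 points and SD 6.7 serve below as the reference.

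**2. Which values would enter the model?** A between-participant variable has one value per person. Usual medicine use at entry fits that description, and so does total medicine use over the trial. Section 3.2 does not choose. The only recording of symptom management that the protocol describes (2.6.2, 2.9, 2.15) is the in-trial log.

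**3. Size if in-trial use is the covariate.** Let pC and pT be the shares using symptom management in the control and intervention arms. Let b be the within-arm difference in UWRI between users and non-users. With a common slope,

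adjusted effect = total effect − b × (pT − pC).

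For power at 32 per arm, with v the average of p(1 − p) over the two arms, the effective SD is the square root of [6.7² − b²v] × [1 + (pT − pC)²/(4v)].

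The documents give none of pC, pT or b. Assumed: pC = 50%, pT from 50% to 20%, b from 0 to −7 points.

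| pT | b | Adjusted effect (true 5.0) | Reduction | Power |
|---|---|---|---|---|
| 50% | −5 | 5 − 5 × 0.0 = 5.0 | 0% | 88.6% |
| 40% | −3 | 5 − 3 × 0.1 = 4.7 | 6% | 80.5% |
| 30% | −5 | 5 − 5 × 0.2 = 4.0 | 20% | 69.3% |
| 20% | −7 | 5 − 7 × 0.3 = 2.9 | 42% | 45.1% |

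With b = 0 the adjusted effect is 5.0 whatever pT is.

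**4. Size if worse symptoms merely prompt use.** Here use has no effect of its own, and its log-odds rise as the UWRI score falls. Results are means of 4,000 simulated trials at 32 per arm, with control use set near 50%.

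| Log-odds per SD of UWRI | Use in intervention arm | Unadjusted | Adjusted |
|---|---|---|---|
| 0 | 50% | 5.00 | 5.00 |
| 0.5 | 41% | 5.00 | 4.73 |
| 1.0 | 35% | 4.98 | 4.16 |
| 1.5 | 31% | 4.99 | 3.65 |

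**5. The same model with a covariate fixed before randomisation.** With half the participants users at entry and users scoring 5 points lower, the mean adjusted estimate is 4.99 against a true 5.00, so there is no bias.

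**The case against.** The strongest reply is that nothing says in-trial values enter the model. One value per person fits usual medicine use or footwear at entry, and adjusting for those is harmless. No section ties the in-trial log to the covariates of section 3.2. This stands as far as it goes: a reader might infer that the treatment effect **is** biased, and the document does not establish that. But the wording does not settle on the harmless reading either, and the session 1 list includes no baseline version of either variable.

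Second, section 2.6.2 tries to hold medicine use at its entry state, and section 2.3 requires agreement to no other treatment. This limits the shift between arms and makes the larger rows above less likely. It does not remove the shift: usual use can rise or fall with symptoms, and the limits on medicines do not cover ice or foam rolling.

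Third, footwear is weak. The default is no change, and replacement is for wear with the same or a similar model. Retraining might alter wear through gait or running volume, but any effect is probably small. This stands.

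Fourth, an unadjusted estimate is reported, and section 3.1 adds direct between-group tests. This also stands, so only the adjusted result is exposed. It protects the conclusion only if the unadjusted estimate is the primary one, which the plan does not say.

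Last, covariate timing may be left to an analysis plan that is not shown. Fine coding may be. Here, though, the protocol itself names the covariates, and the only measurement of symptom management it describes comes after allocation.

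**Conclusion.** The point holds in conditional form. The model names symptom management and footwear as covariates without fixing them before randomisation. If in-trial values are used and treatment affects them, the adjusted effect is not the intention-to-treat effect. Under the assumed inputs, a true 5 points appears as 5.0 down to 2.9 across the grid in step 3, and as 4.7 to 3.7 where worse symptoms merely prompt use.

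The direction towards no difference rests on the assumption that retraining lowers use and that users score worse. If retraining raised use, the sign would reverse. The bias is zero with baseline values or with no treatment effect on use. The sample size and the unadjusted estimate are untouched.

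The documents do not support a claim of certain bias, equal weight on footwear, or any single figure for the size.

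**What to change.** In section 3.2, restrict the treatment-effect model to values recorded before randomisation: baseline outcome, sex, age, BMI and, if wanted, usual medicine use (yes/no) and footwear or orthosis status at entry. Alternatively, drop symptom management and footwear from that model. State which estimate, unadjusted or adjusted, is primary. Report in-trial symptom management and footwear changes descriptively by arm, as co-interventions.

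The cost is a few words of analysis text. Sections 2.6.2 and 2.6.3 imply that usual medicine use is known and footwear is assessed, but section 2.9 does not list either as recorded, so one baseline entry for each may have to be added. The change should be made before outcome data are examined by arm.

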**Methods:**

This study is an assessor‐blinded and participant‐blinded, parallel‐group, randomised controlled trial. The trial will recruit 64 participants aged between 18 and 45 years, with a clinical diagnosis of MTSS that has affected their running participation for at least four weeks. Participants will be randomised to receive best standard care (control) or running retraining and best standard care (intervention group) over an 8‐week period. Best standard care will consist of load management advice, symptom management advice, footwear advice and a strengthening program. Running retraining will consist of a cue to reduce running step length. Outcomes will be measured at weeks 1, 2, 4 and 8. The primary outcome measure will be the University of Wisconsin Running Injury and Recovery Index at week 4. Secondary outcome measures include: (i) Exercise Induced Leg Pain Questionnaire—British Version, (ii) global rating of change scale, (iii) worst pain experienced during a run, (iv) weekly run volume, (v) reactive strength index score, (vi) single leg hop test, (vii) soleus single leg maximum voluntary isometric contraction, (viii) gastrocnemius single leg maximum voluntary isometric contraction, (ix) single leg plantar flexor endurance test, (x) running step length, and (xi) running step rate. Data will be analysed using the intention‐to‐treat principle.

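### The mixed model in section 3.2 makes time a random effect and names no group-by-visit term, so as written it yields a group difference averaged over visits, not the primary week-4 difference

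*Protocol article*

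**What the plan says.** The Methods part of the abstract fixes the endpoint: "The primary outcome measure will be the University of Wisconsin Running Injury and Recovery Index at week 4". Section 2.14 names the same instrument without a week. Section 2.8 places the primary and secondary outcome measurements at "baseline, 2 weeks, 4 weeks, and 8 weeks".

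Section 3.2 gives the model its purpose: "A mixed effects model will be used to assess the mean differences between the groups for the outcomes considered". It describes the fixed effects as between-participant "variables such as age, sex, BMI, symptom management and footwear", and then says "These models incorporate time as the random effects which is a" within-subject variable. On interactions it says only: "Effect modification by age, BMI and sex will be explored using likelihood ratio tests". It names no fixed visit effect, no group-by-visit term and no participant effect, and it does not say which visit the group difference refers to.

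Section 3.1, headed as descriptive, also compares the groups. Differences "for the primary and secondary outcome measures (2, 4, and 8 weeks) will be described and assessed using" t tests for continuous variables, with a Welch-type alternative as a sensitivity analysis. Neither section is named as the primary analysis.

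**The concern.** Visit is a designed factor with three planned post-baseline levels, and the trial's main question concerns one of them. Treating visits as draws from a population of times suits a nuisance factor, but not one whose week-4 level defines the endpoint. Without a group-by-visit term the model returns a single group coefficient. That coefficient equals the week-4 effect only if the effect is the same at every visit or happens to average out to it.

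A constant effect cannot be taken for granted. Under section 2.7 haptic feedback accompanies all runs in weeks 1 to 4, becomes intermittent in weeks 5 and 6, and stops in weeks 7 and 8. The benefit could still be building at week 2, and could persist or fade by week 8.

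Two things are at stake. The estimate reported from the mixed model may answer a different question from the declared primary one. And, depending on how the random part is read, its standard error may be too small.

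**Working it through.** **Inputs from the protocol article.** Effect of 5 points, SD 6.7, power 80%, alpha 0.05, 60 participants and a recruitment target of 32 per group (section 2.4). Outcome visits at baseline and weeks 2, 4 and 8 (section 2.8). The abstract also lists week 1, but section 2.10 describes no questionnaire outcomes at that session, so section 2.8 is followed here.

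**Assumptions, because the document gives no figure.** Two-sided test; within-person correlation rho of UWRI across visits from 0.3 to 0.7; complete data; the effect trajectories shown below.

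**1. The plan's own figure.** d = 5/6.7 = 0.746. A two-sided two-sample t test needs 30 per group, 60 in total, with power 81.1%. At 32 per group, power is about 84%. The stated 60 is reproduced, and it is the sample size for a comparison at a single time point. The calculation therefore fits a week-4 contrast and not a visit-averaged coefficient.

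**2. What the coefficient estimates.** With balanced, complete visits and equal weights, a group effect without a group-by-visit term is the mean of the visit-specific effects. For assumed true effects with 5 points at week 4:

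- Weeks 2, 4, 8 = 2.5, 5, 5: (2.5 + 5 + 5)/3 = 4.2, a shortfall of 0.83/5 = 17%.
- Weeks 2, 4, 8 = 2, 5, 7: 14/3 = 4.7.
- Weeks 2, 4, 8 = 1, 5, 3: 9/3 = 3.0.
- Baseline, 2, 4, 8 = 0, 2.5, 5, 5, if baseline were also a response row: 12.5/4 = 3.1.
- Weeks 2, 4, 8 = 5, 5, 5: 15/3 = 5.0, no discrepancy.

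The size of the gap depends on the trajectory. That the model targets an average does not.

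**3. Standard error if time is literally the only random effect.** A time effect shared by all participants removes visit means but leaves each runner's T scores treated as independent. The model's standard error is then the true one divided by sqrt(1 + (T − 1)rho), and the type I error is 2 × (1 − Phi(1.96 / sqrt(1 + (T − 1)rho))).

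| T | rho | 1 + (T − 1)rho | SE as share of true SE | Type I error, formula | Type I error, simulation |
|---|---|---|---|---|---|
| 3 | 0.3 | 1.6 | 0.79 | 12.1% | 12.6% |
| 3 | 0.5 | 2.0 | 0.71 | 16.6% | 16.4% |
| 3 | 0.7 | 2.4 | 0.65 | 20.6% | 20.8% |
| 4 | 0.3 | 1.9 | 0.73 | 15.5% | 15.6% |
| 4 | 0.5 | 2.5 | 0.63 | 21.5% | 22.1% |
| 4 | 0.7 | 3.1 | 0.57 | 26.6% | 27.1% |

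The simulation used 32 per group, SD 6.7 and 20,000 runs per setting. Analysing participant means, which in balanced data matches a participant random intercept, gave 4.1% to 5.3% (3,000 runs per setting).

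**4. Standard error if the random time effect sits within participant.** A rough simulation with a participant random intercept and time slope (32 per group, SD 6.7, rho 0.5) rejected in 2% to 7% of null trials. At 60 runs per setting, the Monte Carlo error around 5% is sqrt(0.05 × 0.95/60) = 2.8 percentage points. This shows no visible inflation but does not fix the level precisely. The estimand problem in step 2 remains under this reading.

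**The case against.** Four arguments carry weight.

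- **The list of fixed effects is illustrative.** It does not even contain treatment group, which must be in a model meant to compare groups, so it cannot be complete. This stands as far as group is concerned. It does not supply a fixed visit effect: the list gives examples of between-participant variables, while time is called within-subject and explicitly assigned to the random part.
- **Calling time within-subject may mean a random time effect for each participant.** This is a fair reading and perhaps the more natural one. Much of the clustering would then be modelled. A reader might infer from section 3.2 that the trial will run at a type I error near 20%. The text does not support that, because it requires the literal reading with no participant effect at all.
- **Baseline need not be a response.** A reader might infer that the effect is diluted to about 3 points, with a severe loss of power. Under the trajectory of 2.5, 5 and 5 points, that needs baseline as a response row, which the protocol never states. Section 3.1 lists only weeks 2, 4 and 8, and there the same trajectory averages 4.2. Comparing power with a baseline-adjusted week-4 analysis would also mix in a separate gain from the adjustment.
- **Section 3.1 already gives a week-4 t test.** It does, and it matches the sample size calculation. So it would be wrong to say that the protocol offers no route to the week-4 difference. But that test is unadjusted, is one of three time points, stands under a descriptive heading and is not named as primary. It softens the fault in section 3.2 without repairing it.

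It can also be said that covariance structure and visit coding belong in a statistical analysis plan. Leaving them out of an article would be no fault. What section 3.2 does is state a role for time that conflicts with a week-specific endpoint. A later plan would have to inherit that statement or contradict it.

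**Conclusion.** The point holds for the estimand. Section 3.2 as written gives a group difference averaged over visits, while the abstract declares the week-4 difference primary, and no analysis is designated to estimate the latter. The numerical gap cannot be known in advance. It is zero if the effect is constant over visits, 0.8 points out of 5 under the illustrative trajectory of 2.5, 5 and 5, and larger if the effect peaks at week 4.

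The standard-error point holds only conditionally. If no participant-level effect were fitted, type I error would be about 12% to 21% with three post-baseline visits, or 16% to 27% with four visits, for an assumed correlation of 0.3 to 0.7. A participant-level random time effect would avoid most of this. The planned sample size is unaffected: it reproduces as a single-time-point comparison.

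**What to change.** Reword section 3.2, and any analysis plan that follows it, before the data are analysed:

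- Responses: UWRI at weeks 2, 4 and 8.
- Fixed effects: group, visit as a categorical factor, and group-by-visit, with baseline UWRI and sex (the stratification factor in section 2.1) as covariates.
- Within-participant correlation: a participant random intercept or an unstructured covariance.
- Primary estimate: the group contrast at week 4 from this model, with its 95% confidence interval. Section 2.14 should also name week 4.
- The week-4 t test in section 3.1 stays descriptive or supportive, and the text should say so.

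The cost is wording only. Baseline UWRI and sex are already collected at session 1, and no extra visit, measurement or participant is needed.
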